### Confidentiality {27}

No personal identification numbers are recorded in the electronic database, but rather linked to a separate and secure identification list at each site. Part of each national ethical application was an approval of the processes to ensure confidentiality. Each patient receives oral and written information regarding data protection and their rights as a participant in the trial.

### Plans for collection, laboratory evaluation, and storage of biological specimens for genetic or molecular analysis in this trial/future use {33}

No biological material will be collected in this trial.

## Statistical methods

### Statistical methods for primary and secondary outcomes {20a}

Both an intention-to-treat and a per-protocol analysis will be performed. As mentioned, in the primary analysis, survival rates will be compared using the log-rank test. Before analysis, log–log-survival versus time plots will be used to visually assess the assumption of proportional hazards supported by statistical tests based on the inclusion of a time-varying covariate for the treatment effect. In the case of crossing survival curves, the overall log-rank test will be reported together with effect estimates in-between crossings. If repeated crossings occur, this will in itself suggest that the intervention does not result in superior outcomes for the subjects, which will then be reported.

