There are two relevant randomized clinical trials (RCTs), addressing the issue of early TEVAR among TBAD patients. The Acute Dissection: Stent graft OR Best medical therapy (ADSORB) trial, notably underpowered, randomized a total of 61 patients from 17 European centers with acute uTBAD [16]. There were no aortic ruptures at 1 year in either arm of the trial, while TEVAR was associated with improved thrombosis of the false lumen and reduction of its lumen. The Investigaton of Stent Grafts in Aortic Dissection (INSTEAD) trial included 140 patients in the subacute phase [17]. The overall survival at two years was statistically equivalent, 95.6% in the OMT (optimal medical therapy) group and 88.9% in the TEVAR plus OMT group. The long-term results from the extended INSTEAD-XL found a non-significant absolute reduction in all-cause mortality of 8.2% at 5 years for those patients who underwent TEVAR [18]. The authors performed an additional Landmark analysis, thus focusing only on outcomes from years two to five, and identified an absolute mortality reduction of 16.9%.

The conclusions from the retrospective and above-mentioned RCTs have not been persuasive enough for the European Society of Vascular Surgery to render a higher recommendation than “TEVAR may be selectively considered” for those patients presenting with uncomplicated type B aortic dissections [2]. This is furthermore echoed by a recent international survey regarding the preferred treatment of uTBAD, in which 54.8% of respondents answered that they do not routinely use TEVAR, as opposed to 37.4% who prefer this strategy. More importantly, 88.6% of respondents agreed that equipoise was present and that an RCT was needed [19].

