### Sample size {14}

The literature supports an overall estimated 5-year survival for TBAD subjects of approximately 80%, i.e., a 5-year mortality of 20% [33]. The above-mentioned INSTEAD-XL clinical trial identified a reduction in 5-year mortality from 19.3 to 11.1% for those who were randomized to TEVAR, corresponding to a hazard ratio of 0.52 [18]. The estimate was not statistically significant, possibly due to a low sample size.

The primary analysis will be based on the intention to treat principle using the full analysis set and all-cause mortality events as confirmed by the local investigator. The primary objective of the study is to determine the superiority of TEVAR versus SMT in reducing the incidence of all-cause mortality. Assuming a true hazard ratio of 0.52 between TEVAR and SMT, using a two-sided alpha of 5%, 80 subjects with primary endpoint events will provide a statistical power of 80% for the test of all-cause mortality between treatment arms, based on an overall 1:1 allocation between TEVAR and SMT and analyzed with a log-rank test. All Scandinavian countries have registries of vital statistics with a high reliability and almost complete follow-up. Consequently, loss-to-follow-up is expected to be negligible, except for migration, and thus a conservative estimate of loss-to-follow-up is given as 3%.

The study is event-driven. With an estimated annual event rate of 4% for the primary endpoint in the control group and a withdrawal probability of 3%, approximately 550 subjects are estimated to provide the required number of primary events.

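### Repeated crossing of the survival curves is set up as an undefined, uncalibrated sign of non-superiority that can contradict a significant log-rank test

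*Protocol article*

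**What the plan says.** The section on statistical methods for primary and secondary outcomes {20a} states that "in the primary analysis, survival rates will be compared using the log-rank test". Proportional hazards is checked by log-log plots and a time-varying treatment term. Two instructions on crossing follow:

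- Any crossing: "In the case of crossing survival curves, the overall log-rank test will be reported together with effect estimates in-between crossings".
- Repeated crossing: "If repeated crossings occur, this will in itself suggest that the intervention does not result in superior outcomes for the subjects", and this is then to be reported.

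The section on sample size {14} ties the design to the log-rank test: "80 subjects with primary endpoint events will provide a statistical power of 80"%, "based on an overall 1:1 allocation between TEVAR and SMT and analyzed with a log-rank test". The section on interim analyses {21b} also spends alpha through that test only (0.0052 at 40 events, 0.05 at the end).

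The background {6a} gives 2-year survival in the earlier subacute-phase trial as "95.6% in the OMT (optimal medical therapy) group and 88.9% in the TEVAR plus OMT group". The sample size section gives that trial's 5-year mortality as 19.3% without and 11.1% with TEVAR.

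**The concern.** The article fixes two routes to a statement about superiority. The log-rank test has a known error rate and power. The crossing criterion has neither, and the power and alpha statements take no account of it.

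Kaplan-Meier curves cross easily while few deaths have accrued, even when one treatment is better throughout. A trial could therefore reach significance on its primary test and, by following its own text, also report that repeated crossing suggests TEVAR is not superior. Because a crossing is undefined, whether the remark applies can be settled after the curves have been seen.

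The estimates between crossings raise a related problem, because the observed curves choose their windows. Both curves start at 1. If they are equal at times a and b, then S(b)/S(a) is the same in both arms, so the two cumulative hazards over that window are equal. A hazard ratio for any window that closes at a crossing is thus held near 1 by construction. Only the stretch after the last crossing is free. Neither quantity answers the stated objective of survival at 5 years.

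**Working it through.** **Inputs.** From sample size {14}: HR 0.52, two-sided alpha 5%, power 80%, 1:1 allocation, 80 deaths, 277 per arm, control event rate 4% per year, withdrawal 3%. From trial status: 3-year recruitment. Assumed: exponential survival, uniform entry, no stop at the interim. The time span of the 3% withdrawal is not stated, so three readings are shown.

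**The plan's own figures.** Freedman's formula: events = (1.960 + 0.842)² × (1.52/0.48)² = 7.85 × 10.03 = 78.7, so 79. Then 79 × 1.0071 = 79.6, which agrees with the stated 80. Five-year death risk is 1 − 0.96⁵ = 0.185 in controls and 1 − 0.96^(5 × 0.52) = 0.101 with TEVAR, mean 0.1427. Then 79/0.1427 = 554, as stated. The design figures reproduce, and all of them rest on the log-rank test.

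**Crossings when TEVAR works as assumed.** 10,000 simulated trials per column, analysed at 80 deaths. A repeated crossing is at least two sign changes of the Kaplan-Meier difference, ignoring exact ties. A positive trial has two-sided log-rank p < 0.05 in favour of TEVAR. Simulated power is about 0.82.

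Share of positive trials with repeated crossing:

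| Crossings counted | No withdrawal | 3% over 5 years | 3% per year |
|---|---|---|---|
| Every sign change | 23% | 33% | 41% |
| Gaps above 0.1 point | 23% | 22% | 23% |
| Gaps above 0.5 point | 5% | 5% | 5% |
| Gaps above 1 point | 1% | 1% | 1% |
| Every sign change after 6 months | 8% | 15% | 16% |
| Every sign change after 12 months | 3% | 7% | 7% |

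Independent repeats put the top row at 22 to 43% overall. One death moves a curve by about 1/277 = 0.36 point before censoring begins. A gap above 0.5 point therefore means a lead of at least two deaths, and a gap above 1 point a lead of at least three. The rise across the top row comes from near-ties below 0.1 point that withdrawal creates.

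**Do crossings carry information?** Among all trials with 3% withdrawal over 5 years, at least two crossings occur in about 84% when there is no effect and about 39% when HR is 0.52. Counting only gaps above 0.5 point, the figures are 53 to 55% and 8%. So they do carry some.

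**Early risk, later benefit.** The cited figures imply these hazards:

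- Medical therapy: −ln(0.956)/2 = 0.0225 per year to year 2, then −ln(0.807/0.956)/3 = 0.0565.
- TEVAR: −ln(0.889)/2 = 0.0588 per year to year 2, then 0, because 2-year survival of 88.9% equals 100 − 11.1.

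The early excess is 95.6 − 88.9 = 6.7 points. Taking half of it with the same 5-year mortality puts TEVAR survival at 95.6 − 3.35 = 92.25% at 2 years. The TEVAR hazards become −ln(0.9225)/2 = 0.0403 and −ln(0.889/0.9225)/3 = 0.0123 per year. With 3% withdrawal over 5 years, about 71% of positive trials then have repeated crossing, and 31% do above 0.5 point. TEVAR truly improves 5-year survival in this scenario.

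**The case against.** The strongest defence is that this is a reporting remark and not a decision rule. The log-rank test is primary, it is still reported when curves cross, and the remark only says that repeated crossing is suggestive. That stands. A reader might infer that the remark formally overturns the primary test, but the text does not say so. It permits a contradictory interpretation and leaves the conflict unresolved.

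Three other stronger readings are not supported:

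- A reader might infer that about a third of positive trials would be contradicted. That needs every sign change, however small, and the 3% withdrawal that the article calls conservative because loss is expected to be negligible. The article defines no crossing, and its check of proportional hazards is partly visual, so a reading limited to visible gaps is at least as natural. That reading gives about 5% or less under proportional hazards.
- A reader might infer that crossings say nothing about superiority. The comparison with the no-effect case shows otherwise.
- A reader might note that under the earlier trial's full pattern at least one crossing is almost certain (over 99%) and take this as the rate at which the criticised sentence applies. That sentence concerns repeated crossings. A single crossing brings only the log-rank result and the interval estimates.

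A separate analysis plan may handle non-proportional hazards in detail. That does not remove the point, because the article itself states the inference.

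**Conclusion.** The point holds as one of inference and wording. The article fixes an undefined and uncalibrated criterion for non-superiority beside a primary test that alone carries power and alpha, and the two can disagree. How often they would disagree depends mainly on what counts as a crossing, which the article leaves open. Under the design's own HR of 0.52 the range among positive trials runs from about 1% to 43%. It is higher on a given definition if early procedural risk precedes later benefit. The 71% and 31% rest on an assumed half of one small trial's early excess, so they illustrate and do not predict.

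The primary test, event target, sample size and interim boundary are unaffected. Severity is minor to moderate. The assumptions are exponential or two-piece exponential survival, uniform 3-year entry, analysis at 80 deaths and no interim stop.

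**What to change.** 1. Delete the repeated-crossings sentence, or reword it so that crossings are described without any inference about superiority.
2. State that the log-rank result alone decides superiority, whatever the shape of the curves.
3. If the curves cross, report the Kaplan-Meier difference in 5-year survival with a 95% confidence interval, which is the stated objective.
4. Replace estimates between observed crossings with period-specific effects in windows fixed in advance, for example 0 to 2 and 2 to 5 years, the split used in the landmark analysis that the background cites. Label them descriptive, because the later window conditions on survival to 2 years and is not a purely randomized comparison.

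The cost is wording only. The change should be made before outcome data are seen, since an open-label trial with an undefined criterion cannot settle the definition credibly afterwards.

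### Repeated crossing of the survival curves is treated as evidence against superiority, beside the primary log-rank test and with no rule on which of the two prevails

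*Protocol article*

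**What the plan says.** Under Statistical methods for primary and secondary outcomes {20a}, the protocol article states that "in the primary analysis, survival rates will be compared using the log-rank test". It plans log-log plots and a test with a time-varying treatment covariate to check proportional hazards. Two sentences on crossing follow. The first is general: "In the case of crossing survival curves, the overall log-rank test will be reported together with effect estimates in-between crossings". The second concerns more than one crossing: "If repeated crossings occur, this will in itself suggest that the intervention does not result in superior outcomes for the subjects", and it ends by saying that this will then be reported.

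The section does not say how large a crossing must be, when it must occur, or how many make it repeated. It does not say which statement stands if the log-rank test favours TEVAR and the curves also cross repeatedly.

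Under Sample size {14}, the design rests on the log-rank test with equal allocation and a hazard ratio of 0.52: "80 subjects with primary endpoint events will provide a statistical power of 80% for the test of all-cause mortality between treatment arms".

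**The concern.** Both Kaplan-Meier curves start at 100%. With 277 patients per arm, one early death moves a curve by 1/277 = 0.36 percentage points. The order of the curves in the first months therefore depends on which arm has the next death, even when the hazard ratio is 0.52 throughout. Counting crossings gives a swap caused by two or three early deaths the same weight as a late, sustained reversal. It has no controlled error rate, and it says little about whether survival differs overall.

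The trial that supplied the hazard ratio shows that a change of order is compatible with later benefit. According to the Background, its 2-year survival was 95.6% on medical therapy and 88.9% with TEVAR. According to the Sample size section, its 5-year mortality was 19.3% and 11.1%, in favour of TEVAR. That is at least one crossing, not evidence of repeated ones.

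At stake is how the primary result is worded. A significant log-rank test could be published beside a statement that the curves themselves suggest no superiority. What counts as repeated crossing could then be settled after the curves have been seen, in an open-label trial.

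**Working it through.** **Step 1: the plan's own figure.** Inputs from Sample size {14}: hazard ratio 0.52, two-sided alpha 0.05, power 80%, 1:1 allocation, log-rank test. (1.960 + 0.842)² = 7.849.

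- Freedman: 7.849 × (1.52/0.48)² = 78.7, so 79 events.
- Schoenfeld: 4 × 7.849/(ln 0.52)² = 73.4, so 74 events.
- Power at 80 events: 80.6% (Freedman) or 83.3% (Schoenfeld).

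The stated 80 events and 80% power reproduce for the log-rank test.

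**Step 2: how often curves cross by chance.** Inputs from the protocol: 554 patients (Sample size {14}, after the interim inflation factor), control event rate 4% per year, hazard ratio 0.52, 3% withdrawal, three-year recruitment (Trial status). Assumptions: exponential survival with hazards 0.04 and 0.04 × 0.52 = 0.0208 per year, uniform accrual, withdrawal spread as 3% over 5 years, no interim look. Analysis was either at the 80th death or after 5 years per patient, with 10,000 simulated trials per setting. In each trial with a significant log-rank result for TEVAR, the sign changes of S_TEVAR(t) − S_SMT(t) over the death times were counted, ignoring exact zeros.

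| Setting | Log-rank power | Share of significant trials with ≥ 2 sign changes | Power if each such trial were called not superior |
|---|---|---|---|
| 80th death, no withdrawal | 82.1% | 23.1% | 0.821 × (1 − 0.231) = 63% |
| 5 years each, no withdrawal | 80.1% | 22.1% | 0.801 × (1 − 0.221) = 62% |
| 80th death, 3% withdrawal | 81.3% | 33.2% | 0.813 × (1 − 0.332) = 54% |
| 5 years each, 3% withdrawal | 80.7% | 31.8% | 0.807 × (1 − 0.318) = 55% |

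Withdrawal raises the share because the risk sets become unequal. Equal death counts then leave a tiny non-zero difference where there would have been an exact tie. Ignoring gaps below about half a death (0.18 points) brings the withdrawal settings back to 21-22%.

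**Step 3: how far the share depends on the definition.** Among significant trials:

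- three or more sign changes: 10-11% without withdrawal, 20-21% with withdrawal and every change counted;
- crossings that exceed 0.4-0.5 points on both sides: about 5%;
- crossings that exceed 1 point on both sides: about 1%;
- only crossings after year 1: roughly 3-7%.

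The crossings are mostly early. In significant trials with at least two crossings (gaps below 0.18 points ignored), the last one comes at a median of 0.7-0.8 years.

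**The case against.** The strongest defence is that the sentence says only that repeated crossings suggest something. The sentence before it keeps the overall log-rank test in the report, and nothing withdraws that when crossings repeat. The log-rank test is named as primary, powered, and given its final 0.05 level under Interim analyses {21b}. A reader might infer that repeated crossings override a positive test and cancel about a quarter of true-positive trials. The text does not say so: no veto is stated, and a figure near a quarter needs any two sign changes to count, however small. The paragraph concerns visual assessment, where a visible reversal is a natural reading, and visible reversals are rare (about 1-5%).

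A reader might also model three months without any TEVAR effect, which under a veto would take power from 76% to 49%. That is about 13 weeks after randomisation. The protocol requires TEVAR within 12 weeks of symptom onset, so a compliant patient waits less than that.

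Two further points stand. Even as a veto, the sentence could only make a superiority claim harder, so it cannot inflate the type I error. The definition of a crossing may also properly sit in a document not shown.

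The inference itself is not rescued. The phrase "If repeated crossings occur, this will in itself suggest that the intervention does not result in superior outcomes for the subjects" presents crossings as sufficient grounds, and the protocol commits to reporting that conclusion. A definition given elsewhere would narrow when the sentence applies, but would not make it a valid test.

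**Conclusion.** The point holds as a wrong inference with unresolved precedence, not as a stated veto. Under proportional hazards at 0.52, two or more chance sign changes occur in about 22% of log-rank-positive trials. Depending on what counts as a crossing, the share runs from about 1% to about 33%, and the document does not choose within that range. The fall in power from about 81% to about 63%, or to about 55% with withdrawal, is conditional on a veto applied to any two sign changes. It is not the trial's power as planned. The 80 events and 80% power need no correction.

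The figures assume exponential survival, uniform accrual and no interim look. Severity: should-fix. The sentence concerns the conclusion on the primary outcome, but the test, its alpha and the sample size are unaffected.

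**What to change.** Delete the repeated-crossings sentence and state that superiority is decided by the pre-specified log-rank test alone. Report any crossings and the already planned time-varying treatment test descriptively, with the Kaplan-Meier curves and the 5-year survival difference with its confidence interval. If non-proportionality is to inform interpretation, that test is the better basis, because unlike a count of crossings it has a known error rate.

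The cost is one amended sentence, with no added patients or data. It should be made before comparative outcome data are seen. What is lost is an informal safeguard against over-reading a significant test when the curves behave irregularly. The descriptive reporting covers most of that purpose.

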### Interim analyses {21b}

Given the long duration of the study and the potential for achieving sufficient evidence prior to the end of follow-up, as well as the potential for safety issues, a single interim analysis is planned. The interim analysis will be undertaken when approximately half of the total events have occurred, i.e., 40 events. This will use the O’Brien-Fleming boundary with a two-sided significance level of 0.0052 in conjunction with the log-rank test. This virtually preserves the overall type I error rate (4.8% vs. 5.0%), and thus the final analysis at the end of the follow-up will be conducted with the conventional significance level of 0.05 [34].

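### Testing at 0.05 after an O'Brien-Fleming look at 0.0052 gives an overall type I error of 5.2%; the 4.8% cited as the overall rate is the nominal level for the final look

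*Protocol article*

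**What the plan says.** Interim analyses {21b} sets out one interim look. On timing: "The interim analysis will be undertaken when approximately half of the total events have occurred, i.e., 40 events". On the boundary: "This will use the O’Brien-Fleming boundary with a two-sided significance level of 0.0052 in conjunction with the log-rank test". It then draws a conclusion about the final test: "This virtually preserves the overall type I error rate (4.8% vs. 5.0%), and thus the final analysis at the end of the follow-up" is to be "conducted with the conventional significance level of 0.05".

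Sample size {14} fixes the error rate and the event target: "using a two-sided alpha of 5%, 80 subjects with primary endpoint events will provide a statistical power of 80" percent, with the effect given as "Assuming a true hazard ratio of 0.52 between TEVAR and SMT". The parameter list in the same section multiplies the sample size by 1.0071 to allow for the single interim analysis.

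**The concern.** Overall type I error is the probability, under the null, of rejecting at either look. If the final test is run at 0.05, that test alone contributes 5%. A rejection at the interim look that would not have been repeated at the end adds to this, and nothing subtracts from it. So the overall rate must exceed 5%, whatever the timing of the look, and 4.8% cannot be right.

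The figure is recognisable. The pair 0.0052 and 0.048 are the two nominal levels of the classical two-look O'Brien-Fleming design. The sentence labels the second of them as the overall error and then uses it as the reason for not applying it.

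The rule at stake decides the primary endpoint of a superiority trial. A final p between about 0.048 and 0.05 would be declared significant under a procedure that does not hold the 5% set in Sample size {14}. Lowering or defending the threshold after such a p-value had been seen would not be credible.

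**Working it through.** **Inputs.** From Interim analyses {21b}: one look at 40 deaths, interim level 0.0052 two-sided, final level 0.05, stated overall error 4.8%. From Sample size {14}: 80 deaths, overall alpha 5% two-sided, power 80%, hazard ratio 0.52, 1:1 allocation, log-rank test, inflation factor 1.0071. The information fraction is t = 40/80 = 0.5.

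**1. Event count.** Freedman's formula gives (1.960 + 0.842)² × (1.52/0.48)² = 78.7. Multiplied by 1.0071 this is 79.3, which rounds up to 80, so the plan's figure is reproduced. Schoenfeld's formula gives 4 × (1.960 + 0.842)² / (ln 0.52)² = 73.4, i.e. 74.

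**2. Overall error of the rule as written.** Under the null, the log-rank statistics Z₁ (interim) and Z₂ (final) are approximately bivariate standard normal with correlation √t = √0.5. Then

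overall alpha = 1 − P(|Z₁| < c₁ and |Z₂| < c₂),

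with c₁ = 2.794 (two-sided 0.0052) and c₂ = 1.960 (two-sided 0.05). Numerical integration gives 0.05198, and a simulation of 10 million draws gives 0.0519. The stated 4.8% is not reproduced.

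**3. Where 4.8% comes from.** In the classical two-look O'Brien-Fleming design, c₁ = C√2 and c₂ = C, with C solved so that the overall error is 5%. The solution is C = 1.9774, so c₁ = 2.797 (nominal 0.00517) and c₂ = 1.977 (nominal 0.0480). The plan's 0.0052 is the first of these and its 4.8% is the second. The Lan-DeMets O'Brien-Fleming-type spending function would give 0.0031 and 0.0490, so the plan's interim level identifies the classical boundary.

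**4. Sensitivity to timing.** The look is planned at approximately half of the deaths. With the interim level held at 0.0052:

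| Information fraction at the look | Overall error, final at 0.05 | Final level that gives 5.0% overall |
|---|---|---|
| 0.4 | 5.26% | 0.0473 |
| 0.5 | 5.20% | 0.0480 |
| 0.6 | 5.13% | 0.0486 |

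With final 0.048 at t = 0.5, the overall error is 5.00%.

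**5. Consistency with the inflation factor.** The factor is the ratio of the events needed with the look to those needed by a single test at 0.05, for equal power. At 80% power it is 1.0078 for the pair 0.00517/0.0480, and 0.995 for 0.0052/0.05. A factor above 1 is therefore needed only if the final level is reduced. The plan's 1.0071 is the O'Brien-Fleming value at 90% power rather than 80%; the difference is immaterial to the sample size, and the direction is the same.

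**6. Power cost of the stricter final level.** At 80 deaths and hazard ratio 0.52:

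- With Schoenfeld's drift, |ln 0.52| × √80 / 2 = 2.924, power is 83.4% with final 0.05 and 83.0% with final 0.048.
- With Freedman's drift, √80 × 0.48/1.52 = 2.825, it is 80.8% and 80.3%.

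**The case against.** The arithmetic is not in dispute, but its importance can be. The excess is 0.2 percentage points two-sided, or about 0.1 in the direction of a benefit from TEVAR. The section claims only near-preservation of the error rate, not exact control. The data and safety monitoring committee advises the steering committee rather than deciding, so 5.20% is reached only if every interim crossing is acted on as a rejection; otherwise the rate lies between 5.0% and 5.2%. The parenthesis might also be shorthand for a comparison of the correct final level (4.8%) with the conventional one (5.0%), followed by a deliberate choice to ignore the gap. The inflation factor is only indirect evidence, because 1.0071 matches 90% power and not the plan's 80%.

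Much of this is fair as to size. The effect is small, what the authors intended cannot be known, and 0.0480 is exact only for a look at half of the deaths. None of it rescues the statement. On either reading of the parenthesis, the final test at 0.05 takes the overall rate above the 5% in Sample size {14}. The sentence calls 4.8% the overall type I error and rests the choice of 0.05 on it. The inflation factor, whichever power it was computed for, still presupposes a stricter final level. Nor can this be left to a separate analysis plan: the protocol fixes the final level, and a later plan using 0.048 would contradict it.

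**Conclusion.** The concern holds. The rule as written has an overall two-sided type I error of 5.20%, not 4.8%, and 0.0480 is the nominal level that the stated O'Brien-Fleming boundary assigns to the final look. The calculation assumes the usual joint normality of the log-rank statistics, a look at 40 of 80 deaths, and rejection whenever the interim boundary is crossed. That the rate exceeds 5% depends on neither the exact timing nor the approximation to its size. The excess is about 0.2 percentage points and will matter only if the final p falls between about 0.048 and 0.05. Even so, the stated operating characteristic of the primary test is false and is inconsistent with the alpha and the inflation factor in Sample size {14}, so it should be corrected before the interim look.

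**What to change.** Amend Interim analyses {21b} to give three figures: interim two-sided level 0.0052, planned final two-sided level 0.0480, overall two-sided error 5.0%. Delete the statement that the overall error is 4.8% and the inference that the final test can stay at 0.05.

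State 0.0480 as the planned value for a look at 40 of 80 deaths, and add the rule that the final level will be recomputed from the actual numbers of deaths at the interim and final analyses so that the overall error is 5%. If a confidence interval is to agree with the final test, its coverage should match the final level (95.2% at the planned value); the article gives no coverage, so this is a consequence to record and not a correction.

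The cost is one or two sentences in the protocol, with matching text in the analysis plan. Power at 80 deaths falls by about half a percentage point (83.4% to 83.0%, or 80.8% to 80.3% under Freedman's approximation). No more patients or deaths are needed, since the sample size already carries an inflation factor for the interim look.
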